IFN or NAs mono-therapy cannot exert satisfied antiviral effect on CHB patients. Its urgent to take their advantages and disadvantages to improve treatment efficacy and reduce therapy cost. Existing domestic antiviral strategies are mainly based on foreign guidelines, and most clinical research data are limited to mono-therapy. Therefore, new treatment approaches such as optimal combination therapy with the approved antivirals or emerging novel therapeutics integrated viral clearance and immune modulation are needed to establish the Chinese special antiviral strategy toward the functional cure of CHB.

Different characteristics, mechanisms of action and antiviral activities of NAs and IFN provide the possibility of combining these two types of agents for breaking immune tolerance and improving antiviral efficacy for CHB. Our previous prospective, randomized controlled trial (OSST study) which published in Journal of Hepatology reported that switching to 48-week course of Peg-IFN in HBeAg-positive CHB patients who achieved virologic remission after long-term ETV treatment led to significantly increased rates of HBeAg seroconversion (14.9%) and HBsAg loss (8.5%). It received extensive attention from international and domestic liver disease experts and the author was invited to publish a special letter on antiviral treatment strategies for NA-treated patients in the Journal of Hepatology.

Several studies have demonstrated that Peg-IFN combined with lamivudine or adefovir dipivoxil for 96 weeks can obtain higher rates of HBeAg seroconversion and HBsAg seroconversion than the standard duration of 48 weeks, and their safety are consistent. It is suggested that combination therapy of Peg-IFN and NAs are well tolerant and tend to achieve better antiviral treatment efficacy. However, more large-scale multi-center clinical research are needed to further confirm.

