Focusing on increasing the rate of HBsAg loss, the central goal of national "Twelfth Five-Year" viral hepatitis plan, our study proposes a multi-target combination intervention to improve HBsAg loss rate for CHB patients who had received long-term NAs treatment but not achieved HBeAg seroconversion. Based on the data from previous OSST study, the sequential combination therapy of NAs and IFN are designed, and the immunomodulatory factor GM-CSF is added timely. It is planned to establish a cohort in multiple centers and fulfill the new treatment strategy.

This study intends to adopt a prospective, multi-center, randomized, controlled, open-labeled trial design. The enrolled CHB patients will be assigned to three treatment groups according to the principle of random (1:1:1). Patients in Group I are treated with ETV for 96 weeks; patients in Group II are treated with Peg-IFN for 96 weeks, combined with ETV during the first 48-week; Group III are treated with Peg-IFN for 96 weeks, combined with ETV and GM-CSF during the first 48-week. All patients will be followed-up for 24 weeks after treatment. It is expected that the HBsAg loss rate in Group II and III will increase by more than 10% compared with Group I after treatment, which indicates a better clinical outcome. The success of this project will improve the treatment efficacy of existing antiviral therapy, and enable CHB patients to safely stopping NAs in advance to avoid drug resistance. More importantly, amounts of CHB patients with suboptimal treatment efficacy will obtain HBeAg seroconversion even HBsAg seroconversion, which can reduce the occurrence of liver cirrhosis and liver cancer. It will produce huge social and economic benefits.

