## Assignment to treatment groups

All the eligible patients were randomly assigned in a 1:1:1 to one of three groups. We used interactive web response system (IWRS) for computer-generated randomisation sequences with a predefined stratification scheme. Randomisation was stratified by HBeAg (positive or negative) state and gender (male or female) at enrolment. A patient will be enrolled in the study and assigned a patient number after all protocol eligibility requirements have been met. The investigator will use the appropriate patient’s Case Report Form (CRF) and record the patient’s allocated treatment or treatment number in the CRF. It is the investigator’s responsibility to ensure that each patient receives the assigned treatment.

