## Inclusion Criteria

1. Male and female patients aged 18 to 65 years old at baseline;
2. Subjects who experienced ETV treatment for at least 1 year;
3. Serum HBV DNA≤1000 copies/ml;
4. HBsAg positive;
5.
[figure not shown]

[figure not shown]
ALT >2 ULN but <10 ULN and HBeAg positive before NAs treatment;
6. Negative urine or serum pregnancy test (for women of childbearing potential) documented within the 24-hour period prior to the first dose of test drug;
7. Absence of cirrhosis determined by liver ultrasound;
8. Agree to participate in the study and sign the patient informed consent.

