### Efficacy

Efficacy (see Section 5.1 for primary and secondary endpoints) will be determined from assessment of loss of HBsAg, HBsAg positivity and seroconversion, HBeAg loss, HBV-DNA and ALT.

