### Secondary Variables

All secondary variables will be determined at end of treatment and 24 weeks after the end of treatment.

1. HBsAg positivity (defined as presence of anti-HBs) and seroconversion (defined as loss of HBsAg and presence of anti-HBs)
2. Proportion of patients who achieve undetectable HBV DNA
3. Quantitative HBsAg measurement
4. HBeAg seroconversion (defined as absence of HBeAg and presence of HBeAb in

HBeAg negative patients)

1. ALT normalization (defined as ALT measure ≤ ULN)
2. Sustained virologic response at the end of follow-up

Histology improvement (option)

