### Efficacy Analysis

The primary and secondary efficacy analysis will compare efficacy among three groups.

The descriptive statistics depending on the type of variables will be as follows:

Quantitative variable: size, mean, standard deviation, minimum and maximum.

Qualitative, ordinal variables: frequency and percentage per class.

Response rates for primary and secondary endpoints were assessed by calculating percentages and 95% confidence intervals (CIs) for the ITT and mITT populations. Categorical variables were analyzed by the v2 test or Fisher’s exact test, and continuous variables were analyzed by t test or Wilcoxon test as appropriate. Logarithmic transformation was performed in the case of skewed data. Statistical analyses were conducted by SAS version 9.2.

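### HBeAg seroconversion is defined only in HBeAg-negative patients, which leaves out the HBeAg-positive stratum, the patients who can actually seroconvert

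*Protocol*

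**What the plan says.** Under Secondary Variables (section 10.2.2), item 4 reads "HBeAg seroconversion (defined as absence of HBeAg and presence of HBeAb in" and ends "HBeAg negative patients". No other place defines the endpoint. The Synopsis, section 5.1.2 and section 10.1.2 list HBeAg seroconversion without a population.

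Four other places bear on who should be counted:

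- Assignment to treatment groups (4.3): "Randomisation was stratified by HBeAg (positive or negative) state and gender (male or female) at enrolment". Patients of both HBeAg states are therefore randomised, and each patient's state is known.
- Inclusion Criteria (6.3): eligibility requires "HBeAg positive before NAs treatment". Patients who are HBeAg negative at enrolment lost the antigen earlier, on NA treatment.
- Background and Rationale (1): in an earlier trial in HBeAg-positive patients, switching to Peg-IFN "led to significantly increased rates of HBeAg seroconversion (14.9%) and HBsAg loss (8.5"%).
- Background and Rationale (1), on the target of this trial: "CHB patients who had received long-term NAs treatment but not achieved HBeAg seroconversion". No entry criterion enforces this description.

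**The concern.** Seroconversion means losing HBeAg and gaining anti-HBe, so the patients at risk are those who have HBeAg at baseline. Item 4 names the opposite group. A programmer who follows it would select the wrong patients, and the trial would report a seroconversion rate that omits every seroconversion in the HBeAg-positive stratum.

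The Background presents HBeAg seroconversion as one of the benefits expected from the combination. Under the printed rule, the trial could not show that benefit in HBeAg-positive patients. The rate it did report would mix genuine on-treatment anti-HBe gains with antibody that was present before randomisation.

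**Working it through.** The protocol states no rate or power for this endpoint, so there is no figure to reproduce. The check is mainly textual. Arithmetic shows what can and cannot be said about size.

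**Reading 1: HBeAg status at baseline.** The HBeAg-positive stratum falls outside the endpoint. Among baseline-negative patients, the antigen-absent half is met at entry, so response depends on anti-HBe alone. Let

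- a = share of HBeAg-negative patients already anti-HBe positive at baseline (not given in the protocol);
- g = share of the remainder who gain anti-HBe (not given; 0 to 14.9% used, borrowing the Background figure as an upper value);
- d = share withdrawn and counted as non-responders, as Analysis populations (10.2.4) requires for mITT (not given; 0 and 20% used).

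Reported rate = [a + (1 − a)g](1 − d). For example, a = 0.5, g = 0.149, d = 0 gives 0.5 + 0.5 × 0.149 = 0.5745.

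| a | d = 0 | d = 20% |
| --- | --- | --- |
| 0 | 0–15% | 0–12% |
| 0.5 | 50–57% | 40–46% |
| 0.9 | 90–91% | 72–73% |
| 1 | 100% | 80% |

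The result follows a almost entirely, and the protocol does not give a. If the Background's description of the target held for everyone enrolled, a would be 0. Because no entry criterion enforces it, a could be anything.

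**Reading 2: HBeAg status at the visit.** The denominator is then everyone HBeAg negative at that visit: baseline-negative patients who stay negative, plus baseline-positive patients who have lost HBeAg. Among baseline-positive patients, write l for the probability of losing HBeAg and s for the probability of having anti-HBe given that loss. Seroconversion has probability l × s, but this reading gives those patients the rate s. An arm that raised l and left s unchanged would show no benefit among them. Patients who remain HBeAg positive, who are the failures, are removed. The groups compared are no longer those formed by randomisation.

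**The intended population, by comparison.** Among patients HBeAg positive at baseline, a = 0 for every patient by definition, because nobody with HBeAg present meets the endpoint at entry. This is also the population of the 14.9% in the Background.

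**Denominator after correction.** With 257 patients at 1:1:1, each arm has 257/3 = 85.7. The HBeAg-positive share is not given. Assuming 25%, 50% or 75%:

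- 0.25 × 85.7 = 21 per arm
- 0.50 × 85.7 = 43 per arm
- 0.75 × 85.7 = 64 per arm

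**Illustrative power on that denominator.** Take 14.9% against an assumed ETV rate p₂ in a two-sided 5% comparison of proportions: power = Φ[(Δ − 1.96·SE₀)/SE₁], with SE₀ pooled and SE₁ unpooled. For n = 42.8 and p₂ = 5%, Δ = 0.099, SE₀ = √(0.0995 × 0.9005 × 2/42.8) = 0.0647 and SE₁ = √((0.149 × 0.851 + 0.05 × 0.95)/42.8) = 0.0638. Power = Φ(−0.44) = 33%.

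| ETV rate (assumed) | 21 per arm | 43 per arm | 64 per arm |
| --- | --- | --- | --- |
| 1% | 39% | 67% | 84% |
| 5% | 19% | 33% | 47% |
| 10% | 7% | 10% | 13% |

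The ETV rates are assumptions. The only ETV seroconversion figure in the protocol (21%, section 2.2) is for HBeAg-positive patients over 48 weeks, and that section does not describe them as already suppressed on an NA.

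**The case against.** The strongest reply is that this is a one-word slip for HBeAg-positive patients. Item 1 of the same list defines HBsAg positivity by the presence of anti-HBs, which is plainly another drafting error. The endpoint is one of several secondary ones in a self-described pilot, and nothing in the primary analysis depends on it. All of that is fair and limits the severity. It does not make correction optional, because this is the only definition and a literal reading selects the wrong patients.

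A second reply is that the phrase could mean status at the visit and so be merely redundant. That does not stand: as a restriction on who is counted, it removes the failures.

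A reader might also infer stronger points that the documents do not support:

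- *The endpoint sits near its ceiling in every arm.* This needs nearly all HBeAg-negative patients to be anti-HBe positive at entry. The protocol does not say so, and its description of the target points the other way. HBeAg-negative patients without anti-HBe can still gain it on treatment, and counting withdrawals as non-responders lowers the maximum.
- *The Efficacy Analysis section sets a second wrong denominator.* It says "Response rates for primary and secondary endpoints were assessed by calculating percentages and 95% confidence intervals (CIs) for the ITT and mITT populations". That names analysis sets for all endpoints. It does not say that HBeAg-negative patients count as seroconversion successes, nor does it override an endpoint's own population.
- *Section 7.4.1 defines a rival measure.* Its list, "HBsAg positivity and seroconversion, HBeAg loss, HBV-DNA and ALT", says what efficacy is determined from and refers to section 5.1 for the endpoints. HBeAg loss is a component of seroconversion, so this is a minor inconsistency at most.
- *The trial loses a planned comparison with the 14.9%.* No such comparison is planned. That rate came from a 48-week Peg-IFN switch and serves here only to show which population the earlier rate describes.

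**Conclusion.** The definition is wrong as printed. Under the baseline reading it leaves out the HBeAg-positive stratum and credits pre-existing anti-HBe as response. Under the visit reading it conditions on a post-randomisation outcome. This conclusion needs no numerical assumption: it follows from item 4 set against the stratification by HBeAg state and the two Background statements.

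The size of the distortion cannot be computed, because neither baseline anti-HBe prevalence nor the HBeAg-positive share is given. The supportable statement is that the rate is inflated by every HBeAg-negative patient who is already anti-HBe positive at entry. Severity is moderate: one secondary endpoint is affected, while the primary endpoint and the sample size are not.

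**What to change.** Reword item 4 of Secondary Variables along these lines: *HBeAg absent and anti-HBe present at end of treatment and at 24 weeks after it, among ITT/mITT patients who were HBeAg positive at baseline; missing counted as non-response.*

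Name a single baseline assessment, preferably the one used for stratification. HBeAg is measured at screening, up to 8 weeks before randomisation, and again at Day 0, and the two results may differ.

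The change needs no new data. Table 1 schedules HBeAg at baseline, Week 96 and Week 120, and Tables 2 and 3 include anti-HBe in the HBV serology. Table 1 has no separate anti-HBe row, so it is worth confirming that anti-HBe is tested whenever HBeAg is. The price is a smaller denominator and limited power, as shown in the working. Estimates with confidence intervals in this stratum should be presented with that in mind.

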### Sample Size

It was assumed that the HBsAg loss rate would be 3-10% in the IFN arm based on OSST study in NA-suppressed patients, and that HBsAg loss rate in ETV arm would be 0-3%.

But there is a lack of data regarding HBsAg loss rate by the novel treatment strategy using IFN in combination with GM-CSF. As a pilot and a proof of concept study, the sample size was set at approximate 80-100 per group to investigate whether this combination therapy could induce higher HBsAg loss.

### Analysis populations: ITT and mITT population

The ITT population shall include all subjects who receive at least one dose of study medication. For the ITT population, subjects will be analyzed according to the groups to which they were randomized.

A modified ITT (mITT) analysis was conducted, excluding patients who failed to meet inclusion criteria at baseline prior to randomization. Any patients including in mITT analysis who withdrew from the study, for whatever reason, was classified as a non-responder.

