|  | Histology improvement (option) |
| SAFTY: | Adverse events, vital signs and clinical laboratory parameters. |
| PROCEDURES (SUMMARY) | After signing informed consent and meeting screening parameters, patients are randomized to 1 of 3 treatment groups. patients will be evaluated at Day 1, Week 2, 4, 8, 12, 16, 20, 24, 28, 32, 36, 40, 44, 48, 52, 56, 60, 64, 68, 72, 76, 80, 84, 88, 92, 96, 108 and 120. |
| STATISTICAL ANALYSES:  Population: | Intent-to-treat (patients who receive at least one dose of test drug)  Per-protocol (patients who follow the study protocol and complete the study)  All patients receiving at least one dose of study medication and have a subsequent safety assessment will be considered for analyses of safety. |
| Efficacy: | The descriptive statistics depending on the type of variables will be as follows:  Quantitative variable: size, mean, standard deviation, minimum and maximum.  Qualitative, ordinal variables: frequency and percentage per class.  The percentage and 95% CI are employed to serve the calculation of response rates for the primary endpoint and secondary endpoints. The Chi-square test is used for bivariate variables. |
| Safety: | Adverse events   - Adverse events will be assigned preferred terms and categorized into body systems according to the Medical Dictionary for Drug Regulatory Affairs (MEDDRA) classification of the WHO terminology.   Laboratory Safety Data   - The laboratory data will be analyzed according to the   International Conference on Harmonization (ICH) Guideline for Clinical Safety Data Management: Definitions and Standards for  Expedited Reporting (E2). |

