### Exclusion of Data from Analysis

#### Intent-to-Treat Population and modified ITT Population

All subjects randomized will be included in the ITT population.

A modified ITT (mITT) analysis was conducted, excluding patients who failed to meet

inclusion criteria at baseline prior to randomization.

Subjects will be assigned to groups as randomized for analysis purposes.

Subjects will be excluded if they do not meet mITT criteria.

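### ITT is defined both as patients with at least one dose and as all randomised patients, and neither ITT nor mITT is named as the primary set

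*Protocol*

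**What the plan says.** ITT is defined in three places in the protocol.

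- Synopsis, statistical analyses: "Intent-to-treat (patients who receive at least one dose of test drug").
- Analysis populations: "The ITT population shall include all subjects who receive at least one dose of study medication".
- Exclusion of Data from Analysis, in the subsection on ITT and mITT: "All subjects randomized will be included in the ITT population".

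A modified ITT set is also defined, "excluding patients who failed to meet inclusion criteria at baseline prior to randomization". The exclusion subsection then adds "Subjects will be excluded if they do not meet mITT criteria", without saying from which analysis. The synopsis does not mention mITT. Its second population is "Per-protocol (patients who follow the study protocol and complete the study"), which the statistical section never takes up.

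The Efficacy Analysis section reports both sets side by side: "Response rates for primary and secondary endpoints were assessed by calculating percentages and 95% confidence intervals (CIs) for the ITT and mITT populations". No sentence ranks them.

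Two other rules bear on the point. Under Primary Variables, a missing HBsAg result counts as non-response. Under Analysis populations, patients are analysed in the group to which they were randomised.

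**The concern.** The analysis set fixes the denominator of the primary endpoint. Because missing results count as failures, whether a never-treated patient is inside or outside that denominator affects the response rate directly.

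The two ITT rules treat such a patient in opposite ways, and both cannot be programmed. In an open-label trial the choice need not be neutral. Allocation is known before the first dose. Control patients continue a tablet they have already taken for at least a year, while the other two arms are asked to add 96 weeks of weekly injections. Patients who walk away on learning their allocation may therefore come mostly from the Peg-IFN arms. The one-dose rule would remove them after randomisation, in favour of the treatments under test.

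With ITT and mITT unranked, either could be put forward as the main result after the data are seen, and both choices would comply with the text.

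**Working it through.** **1. The definitions compared.** Take a randomised patient who meets the inclusion criteria, takes no study drug and has no Week 96 HBsAg result.

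| Rule | In the denominator? | Counted as |
|---|---|---|
| Synopsis (one dose of test drug) | No | – |
| Analysis populations (one dose of study medication) | No | – |
| Exclusion of Data (all randomised) | Yes | Non-responder |

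The conflict is textual and needs no assumption.

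**2. Who can be lost under the one-dose rule.** According to the overview of study design and the dosing regimen, all three arms take entecavir from day 1: for 96 weeks in the control arm and for 48 weeks in the two Peg-IFN arms. The Analysis populations section asks for one dose of study medication, not one dose of Peg-IFN. A Peg-IFN patient who refuses the injection but takes the assigned entecavir therefore stays in ITT. Only a patient who takes no study drug at all is lost. The synopsis term, test drug, is less clear on this.

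**3. Size of the shift.** Let r be the response rate among all randomised in an arm and u the fraction never dosed, all of them non-responders. The rate among the dosed is r / (1 − u).

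Inputs: r = 8.5% is the HBsAg loss rate quoted in the Background from the earlier switch trial. r = 15% is an assumed value inside the 10-20% given under Numbers of Patients. u = 5% and 10% are assumptions, since the document gives no figure.

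- 8.5% / 0.95 = 8.9%; 8.5% / 0.90 = 9.4%
- 15% / 0.95 = 15.8%; 15% / 0.90 = 16.7%

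The shift is about 0.4 to 1.7 percentage points. With u = 0 the two definitions coincide and the shift is zero.

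**4. Effect on a test.** The synopsis total of 257 gives 257 / 3 = 85.7, about 86 per arm. Assume 9 losses of HBsAg in a Peg-IFN arm and 2 in the control arm, with never-dosed patients only in the Peg-IFN arm.

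| Never dosed | Rates | Difference (points) | Chi-square p | Fisher p, two-sided |
|---|---|---|---|---|
| 0 | 9/86 = 10.5% vs 2/86 = 2.3% | 8.1 | 0.029 | 0.057 |
| 1 | 9/85 = 10.6% vs 2.3% | 8.3 | 0.028 | 0.032 |
| 4 | 9/82 = 11.0% vs 2.3% | 8.7 | 0.023 | 0.029 |
| 9 | 9/77 = 11.7% vs 2.3% | 9.4 | 0.017 | 0.026 |

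Most of the Fisher drop comes with the first patient removed, while chi-square barely moves. That drop is a property of the two-sided Fisher test. With equal arms the mirror-image table counts in the second tail, and with unequal arms it does not. One-sided Fisher moves only from 0.0285 to 0.0272 when one patient is removed. The table shows the drift in the estimate; it does not show that the choice of ITT definition decides significance.

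**The case against.** The strongest reply grants the contradiction but disputes what follows from it.

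- **Refusing the injection.** A reader might infer that a Peg-IFN patient who declines the first injection drops out of ITT. The text does not support this, because such a patient has still received study medication by taking the assigned entecavir. The reply stands, and the route is narrower: withdrawal before any study drug.
- **mITT as an arm-dependent or unlimited exclusion.** A reader might infer this too. The stated criterion is failure of inclusion criteria at baseline before randomisation, eligibility is to be recorded on a screening form, and withdrawals within mITT count as non-responders. The set is not arm-dependent by construction. What remains is that nobody is named to judge eligibility unaware of allocation and outcome.
- **The exclusion sentence.** It could be taken to remove patients from ITT. It sits under a joint ITT and mITT heading after the mITT definition, and its natural meaning is exclusion from mITT. It needs clarifying, but it does not prove that ITT is cut down.
- **Size.** The 5-10% is assumed, the shift is small, and the trial calls itself a pilot and proof of concept. All true.

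A separate analysis plan does not remove the point. This protocol gives its own complete statistical analysis plan, and the conflicting definitions are stated there. The reply limits the size of the problem; it does not reconcile the two definitions.

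**Conclusion.** Wrong as written. The protocol gives two incompatible definitions of ITT, reports the primary endpoint on ITT and mITT without naming the deciding set, and pairs ITT with different second populations in the synopsis and the statistical section. These findings rest on the text alone.

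The possible bias is conditional. It requires patients who take no study drug at all after learning their allocation, more of them in the Peg-IFN arms than in the control arm. That is plausible in this open-label design, but the document neither gives nor implies a number. At an assumed 5-10% in one Peg-IFN arm, and none in the control arm, the Peg-IFN rate rises by about 0.4 to 1.7 points. With no undosed patients it does not change.

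**What to change.** 1. Define ITT once as all randomised patients, analysed as randomised, with missing HBsAg counted as non-response. Name it the primary analysis set.
2. Change the synopsis and the Analysis populations section to match the all-randomised sentence.
3. Label mITT as supportive. Limit it to removing baseline inclusion failures, judged from pre-randomisation data by someone unaware of allocation and outcome.
4. Either carry per-protocol into the statistical section as a supportive set or drop it from the synopsis, so that both list the same populations.
5. Reword the closing exclusion sentence to say that the exclusion is from the mITT analysis.

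The cost is wording, plus a blinded eligibility review for mITT. The Peg-IFN response rates may come out slightly lower than under the one-dose rule.
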